## 1. Study purpose

---

**The aim of the COSMOS-DP trial is to establish the non-inferiority of the safety of resecting the splenic vein together with the pancreatic parenchyma compared with that of the conventional technique of isolating the vein from the pancreas before ligation and division during DP using mechanical staplers.**

The primary endpoint; the incidence of grade B/C PF

The secondary endpoints;

Outcome measures related to surgery; the operative time, blood loss volume, haemostasis of the staple line, integrity of the staple line, incidence of pancreatic injury, need for additional sutures to securely close the pancreatic stump, drainage duration, postoperative hospital stay duration and incidence of conversion from laparoscopic surgery to open surgery.

Outcome measures related to complications; the incidence of all grades of PF, incidence of grade C PF, incidence of intra-abdominal haemorrhage, incidence of all complications, mortality and the incidence of splenic vein thrombosis (1 and 6 months after surgery)

## 2. Backgrounds

---

In general, in distal pancreatectomy (DP) involves not only mandatory dissection of the pancreas but also dissection of the splenic artery and vein. During this surgical procedure, the splenic vein is isolated from the pancreatic parenchyma prior to being ligated and divided. The reason for this is to prevent intra-abdominal haemorrhage from the stump of the splenic vein following the occurrence of pancreatic fistula (PF), which is commonly observed after DP (8.6-42.3%). Although it is relatively easy to isolate the splenic vein at the confluence of the portal and splenic veins, it is often firmly embedded in the pancreatic parenchyma at more distal regions of the pancreas. Furthermore, the splenic vein can be difficult and time-consuming to isolate due to the necessity of carefully handling all small branches that flow from the parenchyma to the splenic vein. Thus, at times, this procedure can lead to hardships, as well as an unexpectedly large volume of blood loss.

More recently, mechanical staplers have been increasingly used to dissect the pancreas, particularly when DP is performed using a laparoscopic approach. Under such circumstances, the splenic vein is often dissected together with the pancreatic parenchyma, with no attempt of isolation. This method of pancreatic dissection has become the standard at some institutions and has been reputed for its apparent technical simplicity. However, PF occurring after this type of resection is of deep concern to surgeons due to the risk of intra-abdominal bleeding from the stump of the splenic vein, which could then be immersed in effusion rich in pancreatic juice.

To date, no scientific investigation of the safety of this useful but potentially hazardous surgical procedure has been performed. Therefore, we plan to conduct a prospective

randomized study to establish the safety of this procedure so that it can be recommended with more confidence. The use of this procedure will likely result in significant reductions in operative time and blood loss during DP.

### **3. Study design**

---

#### **1) Objective**

Patients undergoing open or laparoscopic DP for pancreatic body and tail cancer, intra-ductal papillary mucinous neoplasm, neuroendocrine tumours, mucinous cystic neoplasm, or metastatic pancreatic tumours or similar are eligible for inclusion in this study. In addition, simultaneous resection of the pancreatic parenchyma and splenic vein in one session will be rendered possible through the evaluation of preoperative imaging study findings.

#### **2) Study design**

This study is designed as a multicentre (45 institutes) prospective randomized phase III trial.

#### **3) Arms**

Arm A (separate resection of the splenic vein)

Arm B (combined resection of the splenic vein)

#### **4) Randomization**

Central randomization and registration system will be applied (1:1). Upon randomization, the patients will be stratified by the surgical approach used (open or laparoscopic), institution and thickness of the pancreatic parenchyma (<15 mm or ≥15 mm)

[figure not shown]

## 5) Sample size

304 patients (Arm A: 152 patients, Arm B: 152 patients)

## 6) Statistical analysis

This trial was designed to evaluate the non-inferiority of group B compared with group A in terms of the incidence of PF grade B/C. The incidence of clinically relevant PF (grade B/C) after DP using a stapler has been reported to be 1.9-20.3% in recent clinical trials. Therefore, for an assumed PF incidence rate of 10% with a non-inferiority margin of 9%, the difference of allowable PF incidence rate between groups A and B is 0.09, and the allowable odds ratio is 2.11. When the statistical analysis is performed for a significance level of  $\alpha = 0.05$  (one side) in a non-inferiority design, 138 patients are calculated to be required per arm, with a power  $100(1-\beta)$  of more than 80%, under the assumption that a small number of patients may be deemed ineligible and may thus be excluded from the analysis. Furthermore, as approximately 5% of the patients are expected to be ineligible for surgery as indicated by the laparotomy or laparoscopic findings, the sample size was eventually increased to 304 patients (152 patients per arm).

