(xiii) When a surgeon considers the use of stapler  
as inappropriate

(xiv) Inappropriate for the study objectives

---

\* Anti-coagulant treatment at 24 hrs after surgery is allowed.

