### 5) Allocation

When the case registration is made, the assigned group (A group or B group) and "registration notice form" showing the registration number are displayed. The investigator shall start treatment after completion of registration.

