### 6) Start of the protocol treatment

The research director or the investigator will start the protocol treatment within 28 days after registration after confirming the completion of the case registration with "registration notice form". If it is ineligible, the investigator explains to the subject that registration to this study is not possible.

Registration after the start of protocol treatment is not allowed without exception

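### The protocol lets randomised patients later judged ineligible be left out of the analysis, with the arm already known and no blinding of that decision stated

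*Protocol*

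**What the plan says.** Section 3, item 6 (Statistical analysis) sets the test: "for an assumed PF incidence rate of 10% with a non-inferiority margin of 9" percentage points, one-sided alpha 0.05 and power "of more than 80" percent. It states that "in a non-inferiority design, 138 patients are calculated to be required per arm", on the assumption that "a small number of patients may be deemed ineligible and may thus be excluded from the analysis". A further sentence then adds about 5% for patients found unsuitable once the abdomen is open or viewed by laparoscope, and the total becomes 304 (152 per arm).

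Section 8 fixes the order of events. A patient who does not meet the criteria is not given a registration number (item 4). Item 5 reads "When the case registration is made, the assigned group (A group or B group", and says that this is displayed with the registration number. Under item 6 the investigator "will start the protocol treatment within 28 days after registration".

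Some exclusion criteria in section 4 rest on judgement. Criterion (xiii) begins "When a surgeon considers the use of stapler" and ends with the word inappropriate. Criterion (xiv) covers any patient thought unsuitable for the study's aims. Criteria (ii), vein invasion, and (x), need to resect neighbouring organs, may look different at operation than on imaging.

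Two central checks follow registration: yearly monitoring, which covers eligibility, serious events and deviations (section 6, item 1), and a twice-yearly committee review of photographs taken before and after transection (section 5, item 2). The protocol does not say that either is blind to arm or outcome.

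**The concern.** Ineligible patients are screened out before a number is issued, so every patient judged ineligible afterwards is a post-randomisation exclusion made with the arm known to the investigator. The provision is worded separately from the 5% found unsuitable at operation. It is therefore not confined to patients whose pancreas was never transected, who cannot develop the endpoint. It also leaves room to drop transected patients, who can.

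Such exclusions may not be neutral between arms. The background section describes isolation of an embedded vein as difficult, and that is the Arm A task; that Arm B staples more tissue is a reasonable inference. A judgement that the stapler was unsuitable, or the patient inappropriate, could follow from difficulty that differs by arm and relates to fistula risk. The central checks are periodic and can fall after a fistula is known. If high-risk or affected patients are lost more often from Arm B, the comparison moves towards a false finding of non-inferiority.

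**Working it through.** **Inputs.** From section 3, item 6: 10% in each arm, margin 0.09, one-sided alpha 0.05, power above 80%, 138 per arm before allowance, 152 after. From section 3, item 4: "Central randomization and registration system will be applied (1:1" allocation. The method for the confidence limit is not given; I assume an unpooled Wald limit.

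**The plan's own figure.** n = (1.645 + 0.842)² × (0.10×0.90 + 0.10×0.90) / 0.09² = 137.4, so 138 per arm. This agrees with the protocol. Power at 138: SE = √(0.18/138) = 0.0361; 0.09/0.0361 − 1.645 = 0.847; power 80.2%. At 152 per arm it is 83.4%. The odds ratio (0.19/0.81)/(0.10/0.90) = 2.11 also agrees.

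**Where the decision turns.** Upper limit = (pB − pA) + 1.645 × √[pA(1−pA)/nA + pB(1−pB)/nB]. Non-inferiority requires it to be below 0.09.

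| Arm A | Arm B | Difference | SE | Upper limit | Non-inferior? |
|---|---|---|---|---|---|
| 14/138 | 17/138 | 0.0217 | 0.0380 | 0.0842 | yes |
| 14/138 | 18/138 | 0.0290 | 0.0385 | 0.0923 | no |
| 14/138 | 17/137 | 0.0226 | 0.0381 | 0.0854 | yes |

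The third row is the second with one Arm B patient with an event removed. The Farrington-Manning score test gives the same cut-off at 138 per arm (z = −1.741 at 17 events and −1.544 at 18, against −1.645). With 14/145 in Arm A the boundary lies between 4 and 5 excess events (8.81 and 9.57 points). With 15/152 it is again between 4 and 5 (8.57 and 9.30 points).

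**Range of effect on the one-sided type I error** (exact binomial enumeration of the Wald decision, true rates 10% and 19%). The scenarios are assumptions; the protocol gives no figures for them.

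- *Worst case: only Arm B patients with a known event are removed, 138 per arm at the start.* None removed 5.3%; one 7.3%; two 9.6%; three 13.1%; four 16.6%.
- *Removal before the outcome is known: only Arm B patients, each at double risk (38%), 145 per arm at the start.* None removed 5.4%; three 6.5%; five 7.6%.

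**Numbers that could be left out.** 152 − 138 = 14 per arm (14/152 = 9.2%). The only stated rate is about 5%, and 0.05 × 304 = 15.2 patients.

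**The case against.** The text is a planning assumption and says that patients may be excluded. It is not an analysis rule, and analysis sets are commonly left to a SAP, which is not shown here. That stands in part: a reader might infer that ineligible patients will be dropped, and the protocol does not say so. But a missing definition is not the complaint. The protocol itself provides for the exclusion, and a SAP would have to override it.

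A reader might also infer that operating surgeons remove their own patients. No passage says so. The later checks described are central ones, and section 8 requires criteria to be confirmed before registration. What remains is that the arm is known and no blinding of eligibility decisions is stated at any level.

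The fragility figures could be taken as the expected bias. They cannot be: a decision in theatre removes patients at some risk, not observed events, and the second scenario above shows a modest effect. Nor does the excess of four Arm B events mean that four removals are needed. At 18/138 one is enough; at 26/138, close to a true 19%, nine removals still fail (9.5 points) and ten are needed (8.8 points).

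Finally, 304 − 276 = 28 might be read as a budget of patients to be removed. It includes patients found unsuitable at operation; those without transection cannot have the endpoint, and leaving them out is far less open to bias.

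**Conclusion.** The point holds as a weakness in what the protocol permits. Randomised, transected patients may be excluded for ineligibility after the arm is known, under criteria that partly rest on judgement, with no stated blinding to arm or outcome. The conclusion can depend on a single Arm B event near the boundary. The possible rise in type I error runs from about one or two percentage points (three to five high-risk patients lost before outcome) to about eleven points (four known events removed, 16.6% against 5.3%). The upper end is a worst case. All these figures assume removals from Arm B only, a Wald limit and the protocol's 10% and 19% rates. The documents give no evidence that selective exclusion is intended or has occurred.

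**What to change.** State in the protocol, and carry into any SAP, that:

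- the primary analysis includes every randomised patient in whom the pancreas was transected, in the allocated arm;
- only patients without transection are left out, with counts and reasons reported by arm;
- ineligibility declared after allocation, the photograph review or a change of technique does not remove a patient from this set;
- a per-protocol analysis is required beside it, with exclusions decided blind to outcome (and to arm where feasible), and non-inferiority is claimed only if the two are consistent.

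The per-protocol analysis has to be a required companion because crossovers kept in the primary set can pull the arms together and favour non-inferiority.

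The cost is wording, settled before outcome data are analysed. A few ineligible or crossover patients stay in the primary set, with slight dilution. Sample size is no obstacle (80.2% power at 138 per arm, 83.4% at 152). Leaving out untransected patients avoids a larger dilution: if 5% of 152 per arm were counted as non-events, the margin rates would become 0.95 × 10% = 9.5% and 0.95 × 19% = 18.05%, and the type I error about 6.3% (normal approximation).

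Moving randomisation into theatre is not part of this fix. Allocation at registration, before treatment starts, is an explicit design choice, and changing it would mean rewriting the registration procedure.

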## 7) Enrollment and follow-up period

- Enrollment period: IRB approval-2019/7/31 (3 years)
- Follow-up period: 6 months after final enrollment
- Total study period: IRB approval-2020/7/31

#### 4. Study population

---

##### 1) Objective

Patients undergoing open or laparoscopic DP for pancreatic body and tail cancer, intra-ductal papillary mucinous neoplasm, neuroendocrine tumours, mucinous cystic neoplasm, or metastatic pancreatic tumours or similar are eligible for inclusion in this study.

##### 2) Operative procedure

- Open or laparoscopic DP
- Simultaneous resection of the pancreatic parenchyma and splenic vein in one session will be rendered possible through the evaluation of preoperative imaging study findings.
- Patients indicated for spleen-preserving distal pancreatectomy (SPDP) will be excluded.
- The Warshaw operation (spleen-preserving and splenic artery/vein resection) will be included.
- The extent of lymph node dissection and whether the celiac axis is dissected will be left to the discretion of the surgeons.

##### 3) Inclusion and exclusion criteria

| Inclusion criteria                                                                                   | Exclusion criteria                                                    |
|------------------------------------------------------------------------------------------------------|-----------------------------------------------------------------------|
| (i) Elective open or laparoscopic distal pancreatectomy for diseases of the pancreatic body and tail | (i) Splenic vein-preserving distal pancreatectomy                     |
| (ii) ECOG Performance Status (PS) = 0-1                                                              | (ii) Superior mesenteric vein or portal vein invasion                 |
| (iii) Age $\geq$ 20 years old                                                                        | (iii) Pancreatic trauma                                               |
| (iv) Maintenance of function of the major organs (bone marrow, liver, kidney, lung, etc.)            | (iv) Preoperative inflammatory pancreatic disease (pancreatitis)      |
| (a) White blood cells $\geq$ 2,500/mm                                                    | (v) Requirement of anti-coagulant treatment during or after surgery*  |
| (b) Haemoglobin $\geq$ 9.0 g/dL                                                                      | (vi) Severe ischemic cardiovascular disease                           |
| (c) Platelets $\geq$ 100,000/mm                                                          | (vii) Liver cirrhosis or active hepatitis                             |
| (d) Total bilirubin $\leq$ 2.0 mg/dL                                                                 | (viii) Need for oxygen due to interstitial pneumonia or lung fibrosis |
| (e) Creatinine $\leq$ 2.0 mg/dL                                                                      | (ix) Dialysis due to chronic renal failure                            |
| (v) Sufficient understanding of the study to                                                         | (x) Need for surrounding organ resection                              |

---

provide written informed consent

(stomach, colon, etc.), excluding the left  
adrenal gland and gall bladder

(xi) Active multiple cancer that is thought to  
influence the occurrence of adverse events

(xii) Difficulty with study participation due to  
psychotic disease or symptoms

(xiii) When a surgeon considers the use of stapler  
as inappropriate

(xiv) Inappropriate for the study objectives

---

\* Anti-coagulant treatment at 24 hrs after surgery is allowed.

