### **1) Surgical resection**

Before pancreatic transection, concurrent division of the splenic artery using a mechanical stapler will not be permitted. A linear stapler, Endo GIA Reinforced Reload with Tri-Staple Technology (Black Cartridge, Covidien®), will be used in all patients. The pancreatic parenchyma will be compressed with the stapler at the planned line of resection for over 5 minutes before transection is performed. For the patients in Arm A, the splenic vein will be isolated from the pancreatic parenchyma and dissected after ligation. For those in Arm B, the splenic vein will be transected concurrently with the pancreatic parenchyma using the aforementioned stapler. Anti-coagulant treatment, such as low-molecular-weight heparin or fondaparinux, will be permitted at 48 hrs after surgery.

Antibiotics, plasma expanders, blood products, analgesic drugs, H2 blockers, and proton pump inhibitors will be used for intra- and postoperative management at the discretion of the surgeons. In addition, there are no regulations on the drugs used to control complications and adverse events. Prophylactic administration of octreotide will not be permitted.

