### 1) Monitoring

Central monitoring will be performed each year by the data centre to evaluate the study progress and ensure for study quality. The following aspects will be monitored: i) data accumulation; ii) patient eligibility; iii) severe adverse events; iv) protocol deviations; v) reasons for cessation or expiration of the protocol; vi) background factors of the patients; and vii) other problems concerning study progress and safety.

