#### 6) Incidence of integrity of the staple line

Incidence of insufficient suture on staple line line after pancreatectomy of mechanical stapler

393

394

395

396 7) Incidence of pancreatic injury

397 Incidence of pancreatic injury on staple line during or after pancreatectomy of mechanical stapler

398

399 8) Grade of pancreatic injury

400 Grade of pancreatic injury on staple line during or after pancreatectomy of mechanical stapler

401

402 9) Incidence of additional suture for pancreatic stump

403 Incidence to need additional suture of staple line for hemostasis or repair after pancreatectomy of

404 mechanical stapler

405

406 10) Length of drain placement

407 Number of days from operation date to drain removal date (the peripancreatic drain to be removed

408 last)

409

410 11) Length of the hospital stay

411 Number of days from operation date to discharge date

412

413 12) Incidence of conversion from laparoscopic surgery to open surgery

414 Incidence of conversion to open surgery during laparoscopic surgery

415

416 13) Incidence of overall POPF (Grade A, grade B, and C)

417 Incidence of overall POPF of grade A, grade B, or grade C, according to the ISGPF criteria

418

419 14) Incidence of POPF grade C

420 Incidence of POPF grade C, according to the ISGPF criteria which is the evaluation criteria for

421 POPF

422

423 15) Incidence of postpancreatectomy hemorrhage (PPH)

424 Incidence of overall PPH, according to the ISGPS criteria

425

426 16) Incidence of overall postoperative complications

427 Incidence of overall postoperative complications, according to Clavien-Dindo classification

428

429 17) Incidence of 90-day mortality

430 Incidence of surgery-related deaths from operation date to postoperative 3 months

431

432 18) Incidence of thrombosis of splenic vein

Incidence of thrombosis of splenic vein by follow-up CT or MRI after 1month or 6 months after surgery

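### The exclusion footnote allows anticoagulants at 24 hours after surgery and Section 5.1 at 48 hours, so a start between the two is permitted by one rule and not yet by the other

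*Protocol*

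**What the plan says.** Two current sections of the protocol set a time for postoperative anticoagulants.

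- **Section 4, 3) Inclusion and exclusion criteria.** Exclusion (v) is "Requirement of anti-coagulant treatment during or after surgery". It carries an asterisk, and the footnote reads "Anti-coagulant treatment at 24 hrs after surgery is allowed".
- **Section 5, 1) Surgical resection.** "Anti-coagulant treatment, such as low-molecular-weight heparin or fondaparinux, will be permitted at 48 hrs after surgery".

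Neither statement refers to the other. Neither is limited to an arm, a patient group, or prophylactic as opposed to therapeutic use. The two agents in Section 5.1 are given as examples, so they do not mark off a drug class that the footnote leaves alone.

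Three other places bear on the consequences:

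- Section 6.1 lists "iv) protocol deviations" among the items of yearly central monitoring, next to patient eligibility.
- Section 12 defines a secondary haemorrhage endpoint: "Incidence of overall PPH, according to the ISGPS criteria". Section 1 adds another secondary endpoint, "the incidence of splenic vein thrombosis (1 and 6 months after surgery").
- Section 1 fixes the primary endpoint: "The primary endpoint; the incidence of grade B/C PF".

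**The concern.** Both statements are working instructions to sites, and they give different times. Section 8 has the investigator check the criteria before registering a patient, so the footnote affects who is enrolled. Section 5.1 governs what happens after the operation. A site that enrols a patient under the footnote may then find that the anticoagulant it planned is not yet permitted.

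The timing matters to this trial's question. The stated aim concerns safety, and Section 2 names bleeding from the splenic vein stump as the worry with combined resection. Anticoagulant exposure is plausibly relevant to both haemorrhage and splenic vein thrombosis. The protocol itself chose to regulate it, while leaving most other perioperative drugs to the surgeon. With two written times and 45 institutes, sites could follow different rules in good faith, and the data centre would have no single rule for coding a deviation.

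**Working it through.** There is no plan figure to reproduce. The point does not depend on the error rate, power, margin or sample size. The check is a comparison of the two rules.

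**Inputs**

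- Footnote to exclusion (v), Section 4: 24 hours after surgery.
- Section 5.1: 48 hours after surgery.

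**Step 1: reading.** Both passages say *at* a time. The sensible interpretation is the earliest permitted start. Let t be the hours from surgery to the first anticoagulant dose. The footnote then requires t ≥ 24, and Section 5.1 requires t ≥ 48.

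**Step 2: where the rules agree and where they do not.**

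| Start time t | Section 4 footnote | Section 5.1 | Rules agree? |
|---|---|---|---|
| t < 24 h | not allowed | not permitted | yes |
| 24 h ≤ t < 48 h | allowed | not yet permitted | **no** |
| t ≥ 48 h | allowed | permitted | yes |

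The window of conflict is 48 − 24 = 24 hours wide. If the two passages are instead read as literal time points, 24 and 48 still differ.

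**Step 3: does a division of roles remove the conflict?** Suppose the footnote governs eligibility only and Section 5.1 governs treatment only. A patient who needs anticoagulation from 24 hours is then eligible under Section 4, but may not receive it at that time under Section 5. The conflict remains for that patient.

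**Step 4: who is affected.** Only patients whose anticoagulant would start in the middle row. The protocol gives no count or share. Section 9 lists anticoagulant use among the preoperative parameters, but does not list the postoperative start time, so the share might not be easy to recover from the listed data.

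**Step 5: effect on the comparison.** Both rules apply to Arm A and Arm B. Section 3, 4) stratifies randomization by institution, so a time that a site uses consistently should be roughly balanced between the arms.

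**The case against.** The strongest defence is that the two statements do different jobs: one qualifies an exclusion, the other regulates treatment. A patient can be enrolled under the footnote and then held to the time in Section 5.1, and anyone who starts at or after 48 hours satisfies both. This narrows the conflict to the 24-to-48-hour window but does not remove it.

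The defence is right on several further points, and each blocks a stronger reading that a reader might infer:

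- *That all 304 patients are affected.* This is the planned enrolment to which the rules apply, not the number caught by the conflict. Exclusion (v) narrows the group further.
- *That the non-inferiority result is at risk.* The endpoints concerned are secondary, and nothing in the protocol shows a route from this discrepancy to the grade B/C fistula comparison.
- *That sites will differ, or that staff who know the arm will time the drug accordingly.* The protocol makes both possible and shows neither. Stratification by institution handles stable site habits, though not case-by-case choices or the coding of deviations.
- *That patients would be removed from the analysis.* Deviations are monitored, but no passage names anticoagulant timing as a deviation or excludes such patients.

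Nor does any figure in the protocol size the effect of a 24-hour shift on bleeding or thrombosis.

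**Conclusion.** The inconsistency is real: two operative sections give different times for the same treatment, and nothing in the protocol reconciles them. Its reach is limited to anticoagulant starts from 24 hours up to 48 hours after surgery, in an unstated number of patients. It does not by itself favour either arm. Within those limits it leaves eligibility and deviation coding ambiguous, and it may allow early exposure to vary in a way that matters to two secondary safety endpoints.

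The severity is moderate. The conclusion rests on reading both passages as earliest start times. The protocol does not show which time was intended, and this review takes no position on that.

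**What to change.** Reconcile the footnote to exclusion (v) with Section 5.1 so that a single time, chosen by the clinical team, appears in both places. State that it is the earliest permitted start, if that is what is meant, and that it applies identically in both arms. Use that same time when eligibility is checked and when deviations are coded at central monitoring.

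The cost is a one-line amendment, submitted to the review boards under Section 13, 1), and a notice to sites. The sample size and the primary analysis do not change.
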